### Assessment

Table 3 displays all quantitative measuring instruments together with their assessment time points over the course of the study.

In the selection of the measuring instruments, particular attention was paid to the objectivity, reliability, and validity of the assessments. The methods employed in this study encompass clinical interviews, questionnaires, cognitive tests and semi-structured qualitative interviews.

**Table 3 Tab3:** Overview of descriptive data, quantitative outcomes and screening tools (with instruments and assessment time points)

Assessment Schedule	T0	T1	T2	T3	T4	T5	T6	T7
Informed Consent	x							
Allocation	x							
**Interventions**								
VISION-AGE IG								
CG								
**Inclusion/exclusion variables**								
• Personal contact data	x							
• Sociodemographic variables	x							
• Mental and physical comorbidities, medication	x							
• Depression and anxiety symptoms (HADS)	x							
• Modified Clinical interview for depression (based on DIPS)	x							
• Cognitive function (MMST)	x							
**Primary outcome**								
• Depression symptoms (PHQ-9)		x	x	x	x	x	x	x
**Secondary outcomes**								
• Clinician-Rated depression Symptoms (MADRS)		x					x	x
• Anxiety (GAS)		x					x	x
• Psychological Well-being (SPWB)		x					x	x
**Mediator variables**								
• Self-directed ageism (Subscale self-directed ageism, WHO Ageism Scale, expanded by four items)		x	x				x	x
• Ego-Integrity (NEIS)		x		x			x	x
• Selection Optimization Compensation (SOC)		x			x		x	x
• planning behaviour (based on the PFC)		x				x	x	x
**Further exploratory measures**								
• Working Alliance (WAI-SR)					x			
• Group Cohesion (FEPiG)					x			
• Programme Satisfaction (ZUF-8)							x	x
• Pre-programme: Assessment of individual therapeutic goals (across five categories); Post-programme: Goal attainment scale		x					x	x
• Assessment of medical resource utilization (self-developed questionnaire)		x					x	x
• Health-related life quality (EQ-5D-5L)		x					x	x
• Acceptance of video technology (TUQ)			x	x	x	x	x	x
• Assessment of health-related changes (self-developed questionnaire)		x	x	x	x	x	x	x
**Safety relevant data**	Notification is possible at anytime.							

Note. **T0** = Enrolment, afterward Allocation, **T1** = Baseline assessment, **T2–T5** = intermediate assessment, **T6** = post-treatment assessment, **T7** = FU assessment

The data collection will be conducted on seven time points to assess the short- and medium-term effects of the VISION-AGE-intervention, and will be identical for both the IG and CG. The assessment points include:

A baseline assessment prior to the start of the intervention;Following completion of the first module (Positive self-perceptions of ageing, i.e., group session 4);Following the second module (Life-review, i.e., group session 10);Following the third module (Life-management, i.e., group session 15);Following the fourth module (Life-planning, i.e., group session 19);Two weeks after the end of the programme (i.e., group session 20); and Six months post-programme (FU).

To encourage continued participation, the study participants receive greeting cards, which include memories of the group sessions, once they have completed all six assessment points.

### Primary outcomes

The primary outcome variable is the reduction in participants’ depressive symptoms, as indicated by changes in their self-reported scores on the Patient Health Questionnaire-9 (PHQ-9) [45] between pre- and post-treatment (T1–T6) and FU (T1–T7). The PHQ-9 is recorded at each measurement point T1–T7.

### Secondary outcomes

As secondary outcomes, changes from baseline (T1) measurement to posttreatment (T6) and FU (T7) will be examined in the following concepts:

A reduction in clinician-rated depressive symptoms will be assessed using the Montgomery-Åsberg Depression Rating Scale (MADRS) [46];A reduction in anxiety symptoms will be assessed using the Geriatric Anxiety Scale (GAS) [47]; andAn improvement in psychological well-being will be assessed using a short version the German short version of Ryff’s scales (SPWB) [48].

### Mediator variables

The following concepts of self- and developmental regulation strategies will be assessed as mediator variables at baseline (T1), at one of the four intermediate time points, after the completion of the respective module, at post-treatment (T6), and at FU (T7):

Positive self-perceptions of ageing, fostered in Module 1, will be assessed as the inverse of the score on the self-directed ageism subscale of the World Health Organization (WHO) Ageism Scale (translated into German by the research team) [49] and is further expanded by four additional survey items on ageism [50];Reminiscence, fostered in Module 2, will be assessed as ego-integrity by using the short version of the Northwestern Ego Integrity Scale (NEIS; translated into German by the research team) [51];Life management, fostered in Module 3, will be assessed using the Scale Selection Optimisation Compensation (SOC) [52]; andFuture planning, fostered in Module 4, will be assessed using a modified 6-item scale based on the Preparation for Future Care Needs – 5-item Short Scale (PFC; translated into German and modified by the research team) [53].

### Further exploratory measures

For exploratory purposes, following variables on specific group dynamics will be recorded at T4:

The therapeutic alliance, as rated from the perspectives of both the patient and the group therapists or group facilitators, will be assessed using the Working Alliance Inventory-Short Revised (WAI-SR) [54] andGroup Cohesion will be assessed using the Scale for the assessment of therapeutic processes in group therapy (FEPiG) [55].

Moreover, post-treatment (T6) and FU (T7), the general satisfaction of participants with the programme will be assessed using the Patient Satisfaction Questionnaire (ZUF-8) [56]. At baseline (T1), participants are supported in formulating SMART (specific, measurable, attractive, realistic and time-bound) individual therapy goals in five categories. At the post-treatment (T6) and FU (T7), participants will be asked to rate their progress towards these goals using a Goal Attainment Scale designed by the research team based on that of Wilz and colleagues. Additionally, participants’ assessment of medical resources utilization (health- and care-related treatments and assistive devices) will be assessed using a self-developed questionnaire at baseline, as well as at post-treatment and FU, so each measurement occurring approximately six months apart. At the same three points (T1, T6, T7) health-related life quality is assessed by using the EuroQol 5 Dimensions, 5 Levels Questionnaire (EQ-5D-5L) [57]. Acceptance of video technology is assessed at each measurement point (T2–T7) after the start of the programme by using the Telehealth Usability Questionnaire (TUQ) [58]. Changes in medication and new diagnoses made by participants’ outpatient physicians are inquired about at each assessment point.

### Planned statistical analyses

Participants who attend fewer than 75% of sessions (i.e. fewer than 15 group sessions and fewer than three individual sessions) will be excluded from the per-protocol analysis. To prevent an attrition bias, intention-to-treat analyses are used. Missing data will be handled using multiple imputation.

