### Intervention

Participants will find out in the first group session whether they have been assigned to the IG or the CG. Both programmes include 20 weekly online group appointments (with each session lasting 100 min, including a 10-min break) in a fixed group of four, as well as four additional individual meetings with group therapist (in the IG) or group facilitator (in the CG). Participants must join the meetings using their own devices, such as personal computers or tablets. If more than two participants permanently withdraw from a therapy group (e.g., due to illness or lack of motivation), the remaining participants will be offered the opportunity to switch to another group.

To prevent bias and buffer against potential investigator allegiance effects, group therapists and group facilitators are not part of the research team and do not conduct measurements with the participants. They are trained in a two-day pre-intervention workshop to ensure adherence to the respective manual and are regularly supervised by the research team based on session videos. In order to verify the integrity of the treatment, a sample of 10% of all sessions is evaluated by raters who are unaware of the study hypotheses, condition, and session number. Thereby adherence to the study protocol is evaluated using a 20-item adherence scale derived from the two manuals (10 Items IG, 10 Items CG). In addition, the session-documentation is regularly checked for manual-consistency.

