### Intervention-group VISION-AGE

VISION-AGE is a standardised, age-sensitive group psychotherapy programme carried out via video conference by trained psychotherapists. The treatment manual was tested in the psychotherapeutic university outpatient clinic of the MSB Medical School Berlin during a three-year pilot phase and was refined in an iterative process based on clinical experiences and patient feedback. There was no evidence of any negative therapy effects. The manual focuses on promoting self- and developmental regulation strategies and thereby addresses the three biographical ‘time corridors’ past - present - future. Well-established LRT methods are enriched by CBT and PP techniques. In addition to the 20 group sessions, four individual sessions (each 45 min long) are intended to reinforce the therapeutic alliance and deepen the content of the group sessions. The initial upstream module focuses on reflecting upon and modifying existing images and experiences of ageing, as well as addressing ageism, in order to build the motivation necessary for change (Module 1 Positive self-perceptions of ageing), followed by Module 2 Life-review, Module 3 Life-management and Module 4 Life-planning. An accompanying handbook is sent to participants prior to the intervention, providing preparatory tasks related to specific sessions of the manual (e.g. collecting photos for the LRT sessions or a gratitude exercise for the Life-management sessions). For an overview of the therapeutic manual’s contents and the postulated mechanisms of action, see the supplemental material.

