### Control group

The active CG is a non-clinical group discussion programme designed to provide social support and stimulation through group discussions in a supportive, non-judgemental environment. During the first half of each session, participants discuss personal, everyday issues from the previous week, followed by a discussion of stimulating, neutral topics such as hobbies, cooking, or animal companionship. Group facilitators encourage engagement and socialisation among group members, similar to the type of support participants might receive in a community support group at a senior citizens’ centre. The manual is based on one used in a previous study [36], where it showed a small positive effect on depression and anxiety in older patients, and has been adapted and expanded for the present study. The CG programme will be delivered by senior assistants, as the work requirements align with their usual work tasks and no clinical skills are necessary. To achieve the same therapeutic dosage as the IG, the time allocated to group therapy sessions is identical to that of the IG. In terms of individual contact, participants will receive four five-minute friendly digital meetings with their group moderator, as well as four additional 40-minute audio features offering stimulating content related to the preceding sessions (e.g., about the benefits of having an animal companion). See the supplemental material for an overview of the group discussion manual, including the discussion topics.

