### Statistical analysis sub-study 1 (quantitative study)

Statistical analyses regarding sub-study 1 will be based on intention-to-treat (ITT) as well as on per-protocol analyses. The primary analysis will be ITT. To compensate for panel attrition and item-nonresponse, missing data will be multiply imputed in all ITT analyses. Imputation models will be fully compatible to the subsequent analysis models (i.e., substantive model compatible multiple imputation) and will include all relevant associations (like interaction terms) and will represent the clustered structure of the data. The main substantive model of interest is a (generalized) linear mixed effects model, which evaluates stability and change in the outcome variables over time depending on experimental condition. The focal effect of interest in this model is the time by condition interaction. To interpret this effect, we especially look at the following contrast: the pre to post change in the experimental condition in comparison to the pre to post change in the control condition (i.e., a contrast over two contrasts). Additionally, pre-post and pre-FU effect sizes (Cohen’s d) will be calculated for all outcome-variables for both groups (IG and CG) to further quantify the found effects. In additional (exploratory) analyses, we will test for possible effects of gender, age, education, comorbidity and severity of comorbid symptoms. We also explore possible interactions of the outcome variables by means of parallel longitudinal path modelling. If the first two hypotheses can be confirmed, hypothesis 3 (regarding the underlying therapeutic mechanisms) will be evaluated by mediation and moderation analyses using path models.

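### The per-protocol exclusion contradicts itself: a 75% attendance criterion is spelled out as two limits joined by *and*, so meeting either one keeps a participant in

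*Protocol article*

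**What the plan says.** Under Planned statistical analyses, the criterion is first given as a percentage: "Participants who attend fewer than 75% of sessions" are those who "will be excluded from the per-protocol analysis". A parenthesis opening with i.e. then turns the percentage into counts: "fewer than 15 group sessions and fewer than three individual sessions".

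The denominators are in the Intervention section: "Both programmes include 20 weekly online group appointments", plus four individual meetings in each arm. Those meetings differ in length. The section on the VISION-AGE arm gives 45 minutes for each one. For the control group, "participants will receive four five-minute friendly digital meetings with their group moderator", supplemented by four 40-minute audio features.

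The section on sub-study 1 says that its analyses "will be based on intention-to-treat (ITT) as well as on per-protocol analyses", and names ITT as primary. The per-protocol rule is not restated or corrected anywhere else in the article.

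**The concern.** The limits are conditions for *leaving* the set. Joined by *and*, they remove a participant only when both counts are short. The explanation is therefore weaker than the criterion that it explains, and someone well under 75% can remain.

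The per-protocol analysis is meant to show the effect among participants who received an adequate amount of the programme. If the parenthesis goes into code as written, the set will contain participants who did not, and it will not be the set that 75% of sessions promises. The error also certifies different exposure in the two arms: three individual contacts are enough to stay in, and these amount to 135 minutes in one arm and 15 in the other.

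**Working it through.** **Inputs.** 20 group sessions and four individual sessions (Intervention); the 75% criterion and its two counts (Planned statistical analyses); contact lengths of 45 and 5 minutes (the two arm descriptions).

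**1. The plan's own figures.** 0.75 × 20 = 15 and 0.75 × 4 = 3, so both counts reproduce exactly. On all sessions together, 0.75 × 24 = 18.

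**2. What the written rule does.** Group attendance can be 0–20 and individual attendance 0–4, giving 21 × 5 = 105 patterns.

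- Excluded (group below 15 *and* individual below 3): 15 × 3 = 45. Retained: 105 − 45 = 60.
- Retained with both limits met: 6 × 2 = 12. Retained with one limit missed: 60 − 12 = 48.
- Of those 48, below 18 of 24: 29 with group attendance short (15 with three individual sessions, 14 with four) and 6 with individual attendance short (15+0, 15+1, 15+2, 16+0, 16+1, 17+0). Total 35.
- The highest excluded total is 14 + 2 = 16, so nobody at or above 18 is removed. The error runs one way only.

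Examples that stay in: 0 + 3 = 3/24 = 12.5%; 10 + 3 = 13/24 = 54.2%; 15 + 0 = 15/24 = 62.5%.

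**3. Exposure behind three individual contacts.** VISION-AGE arm: 3 × 45 = 135 minutes. Control group: 3 × 5 = 15 minutes, not counting the audio features.

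**4. What each repair retains.**

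- *Or* rule (at least 15 group and at least three individual): 12 patterns, the lowest being 15 + 3 = 18/24 = 75%.
- At least 18 of 24: 12 + (48 − 35) = 25 patterns.
- Group sessions alone, at least 15: 6 × 5 = 30 patterns.

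The first two differ on 25 − 12 = 13 patterns, for example 14 + 4 and 20 + 2.

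**5. How many people this might be.** Patterns are not patients, and the article gives no attendance distribution, so what follows rests on assumptions. Let G = P(group ≤ 14) and I = P(individual ≤ 2). With A the probability of missing both limits and O = G + I − A that of missing at least one, the written rule keeps the share (O − A)/O of those who miss at least one.

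*All sessions independent*, attendance probability p, so A = G × I (results from unrounded values):

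| p | G | I | A | O | kept |
|---|---|---|---|---|---|
| 0.80 | 0.196 | 0.181 | 0.035 | 0.341 | 90% |
| 0.75 | 0.383 | 0.262 | 0.100 | 0.544 | 82% |
| 0.70 | 0.584 | 0.348 | 0.203 | 0.729 | 72% |

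*Attendance correlated within person*: each participant has an own attendance probability, drawn from a beta distribution with mean m and intra-person correlation ρ, that is Beta(m(1−ρ)/ρ, (1−m)(1−ρ)/ρ), shared by both session types:

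| m | ρ = 0.1: A, O, kept | ρ = 0.6: A, O, kept |
|---|---|---|
| 0.80 | 0.115, 0.366, 69% | 0.204, 0.279, 27% |
| 0.75 | 0.181, 0.490, 63% | 0.257, 0.345, 25% |
| 0.70 | 0.259, 0.608, 57% | 0.311, 0.408, 24% |

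Under the same correlated model, the written rule keeps about 19–59% of those below 18 of 24 sessions.

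**The case against.** The strongest reply is that *and* merely lists the two converted limits, the percentage governs, and no statistician would run the literal rule. That is a plausible account of what the authors meant. It does not settle the matter: dropping the literal reading still leaves two incompatible rules, exclusion for missing either limit or exclusion below 18 of 24.

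Second, this is a superiority trial with ITT as the primary analysis, and the sample size does not rest on the per-protocol set. This stands in full, and it limits the seriousness of the point.

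Third, drop-out shortens both counts together, so independence exaggerates the leak. This also stands. Under one illustrative scenario (20% drop out at a uniformly distributed time, 92% attendance otherwise, individual meetings spread through the programme), the written rule excludes 15.3% against 20.1% under *or*. It keeps (20.1 − 15.3)/20.1 = 24% of those missing a limit, and only about 1.4% of all participants stay in with fewer than 18 sessions. A reader might infer from the independent-sessions figures that the rule keeps most under-treated participants and that the per-protocol set drifts towards ITT. The article does not support that. Missing one limit is also not the same as low attendance: 20 + 2 is 22/24 = 92%.

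Fourth, the difference in contact length is a design feature, and an *or* rule does not remove it: a control participant with all 20 group sessions would be excluded for missing two five-minute meetings. That is fair, and it is a reason not to treat *or* as the only repair.

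**Conclusion.** The rule is wrong as written. The percentage and the counts that explain it define different sets, nothing else in the article reconciles them, and the literal version errs only towards keeping low attenders. This is a stated rule in conflict with itself, so it is not a detail left to an analysis plan.

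The logical defect needs no assumption. Its size in patients does, and cannot be computed from the article. With mean attendance of 70–80%, the share kept among those missing at least one limit is about 24–69% for within-person correlation of 0.1–0.6. The 72–90% range requires independent sessions, which is unlikely when drop-out is expected.

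The point should be fixed, but it does not threaten the primary conclusion. A reader might infer that the main result is at risk, or that *or* is plainly what the authors intended; the documents support neither.

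**What to change.** Before any outcome data are seen, restate the rule so that the words and the counts agree, choosing one of:

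- replace *and* with *or*, so that inclusion needs at least 15 group and at least three individual sessions;
- apply 75% to all 24 sessions, so that inclusion needs at least 18;
- apply 75% to the 20 group sessions alone (at least 15). Group session time is identical in the two arms, so this choice avoids counting 45-minute and five-minute contacts as equal. The text should then say that the percentage refers to group sessions, since 15 + 0 would stay in.

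The authors must say which they mean, because the first two already disagree on 13 attendance patterns. The change is a word or a short sentence in the protocol, carried into the analysis plan. Its cost is a somewhat smaller per-protocol set than the literal rule gives; the primary analysis and the sample size are untouched.

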### Statistical analysis sub-study 1 (quantitative study)

Statistical analyses regarding sub-study 1 will be based on intention-to-treat (ITT) as well as on per-protocol analyses. The primary analysis will be ITT. To compensate for panel attrition and item-nonresponse, missing data will be multiply imputed in all ITT analyses. Imputation models will be fully compatible to the subsequent analysis models (i.e., substantive model compatible multiple imputation) and will include all relevant associations (like interaction terms) and will represent the clustered structure of the data. The main substantive model of interest is a (generalized) linear mixed effects model, which evaluates stability and change in the outcome variables over time depending on experimental condition. The focal effect of interest in this model is the time by condition interaction. To interpret this effect, we especially look at the following contrast: the pre to post change in the experimental condition in comparison to the pre to post change in the control condition (i.e., a contrast over two contrasts). Additionally, pre-post and pre-FU effect sizes (Cohen’s d) will be calculated for all outcome-variables for both groups (IG and CG) to further quantify the found effects. In additional (exploratory) analyses, we will test for possible effects of gender, age, education, comorbidity and severity of comorbid symptoms. We also explore possible interactions of the outcome variables by means of parallel longitudinal path modelling. If the first two hypotheses can be confirmed, hypothesis 3 (regarding the underlying therapeutic mechanisms) will be evaluated by mediation and moderation analyses using path models.

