### Power and sample size

The study will aim to include 250 participants, with 125 allocated each to the IG and the CG, thereby ensuring a minimum of 100 completed data sets for each intervention at the FU. The plan is founded upon a priori sample size calculation, which yielded a total of 200 participants following a 1:1 randomisation ratio. However, the drop-out-rate must also be considered, which is estimated at 20%, based on the findings of previous studies, for example, 17% in a study with older adults experiencing depression and anxiety [36].

The sample size calculation is based on the assumption of a medium-to-large pre-post (“within”) effect size (d = 0.75) for VISION-AGE and a moderate “between” effect size (d = 0.45) for the contrast (pre-post change in the IG compared to pre-post change in the CG). It is hypothesised that the proposed programme, considered an enhanced form of LRT, will demonstrate effect sizes that are at least commensurate with those observed in LRT, and approximately equivalent to those reported for CBT: The large pre-post effect size, as found for CBT (d = 1.06) and LRT (d = 1.0) in late-life depression [16] will somewhat be reduced due to the possible comorbidity with anxiety and the video-based format (e.g., g = 0.79 for depression and g = 0.82 for anxiety, meta-analysis) [33]. The group setting additionally reduces the effect size in late-life depression (e.g., d = 0.65) [39]. However, since we are planning very small groups and additional individual sessions, we estimate a within effect size of no less than d = 0.75 and a between effect size of d = 0.45.

For statistical tests on the α = 5% level, with a total sample size of *N* = 200 (100 per arm), power simulations using R package Superpower [40] yielded a power > 0.90 for both main effect and the interaction regarding a 2 (condition) by 2 (time) mixed Analysis of variance (ANOVA), as well as power > 0.80 for the main contrast of interest (i.e., the pre-post change in the IG in comparison to the pre-post change in the CG).

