During enrolment interviews, participants are asked to provide personal (contact) details such as age, address and phone number. In addition, information on pre-existing mental and physical comorbidities, current medication as well as relevant socio-demographic variables, is requested. Self-report measures of depressive and anxiety symptoms are collected via the Hospital Anxiety and Depression Scale (HADS) [42]. A HADS score of ≥ 8 is considered clinically relevant for the depression subscale, while a score of > 18 on either the depression or anxiety subscale indicates a very severe manifestation of that subscale. Depressive symptoms of clinical severity (i.e. a score of ≥ 4 on a 0–8 scale) and associated diagnoses are assessed using the section depression from the Diagnostisches Interview bei psychischen Störungen (Structured Clinical Interview for Mental Disorders, DIPS) [43], slightly adapted for the purpose of present study. Cognitive function is assessed using a slightly adapted version of the Mini Mental Status Test (MMST) [44], a screening tool for cognitive impairment. A score of MMST < 25 is considered to be (mild) cognitive impairment. An indication for participation in group therapy is assessed in the clinical impression, based on the assessment of whether the individual person with their symptoms, themes and personality could benefit from group exchange. Participants are assumed to have a stable internet connection and basic IT skills if they can register independently, provide digital informed consent and attend the enrolment interview.

Finally, the severity of the depressive disorder (mild or moderate) and the presence or absence of anxiety symptoms are assessed based on clinical judgement after all enrolment diagnostics have been carried out.

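### Adjusting the primary contrast for T1 PHQ-9, or imposing a common T1 mean, would add precision at no cost; the article states neither

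*Protocol article*

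**What the plan says.** The section Statistical analysis sub-study 1 (quantitative study) names a (generalized) linear mixed model. Its focal effect is the interaction of time and condition, interpreted through one contrast: "the pre to post change in the experimental condition in comparison to the pre to post change in the control condition". Gender, age, education, comorbidity and severity of comorbid symptoms appear only under additional exploratory analyses. T1 PHQ-9 is not listed as a covariate, and nothing is said about whether the arms share a T1 mean.

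Power and sample size uses the same contrast. The calculation "yielded a total of 200 participants following a 1:1 randomisation ratio", with "a between effect size of d = 0.45", and reports "power > 0.80 for the main contrast of interest" from a mixed ANOVA with two conditions and two times.

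Randomization and blinding specifies simple randomisation. Table 3 schedules the PHQ-9 at T1 to T7, and the MADRS, GAS and SPWB at T1, T6 and T7. At enrolment, "the severity of the depressive disorder (mild or moderate) and the presence or absence of anxiety symptoms are assessed" as well (Inclusion criteria and accompanying measurement).

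**The concern.** Under randomisation the arms have the same expected T1 score. Subtracting T1 fixes its coefficient at 1, whereas adjustment estimates that coefficient from the data. In large samples adjustment is never less precise, and it is usually more precise. A two-by-two mixed ANOVA tests its interaction exactly as a t-test on change scores would, so the contrast as powered is the subtracting kind.

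A difference of changes also over-corrects a chance T1 difference between the arms, and simple randomisation does nothing to keep that difference small. At stake is power that could be had from data the trial already collects.

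**Working it through.** **Inputs from the article (Power and sample size).** 100 analysed per arm; between-arm d = 0.45; "For statistical tests on the α = 5% level" (sidedness not stated, two-sided assumed).

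**Inputs not in the article (assumed).** The pre-post correlation r, the ratio k of post to baseline SD, and the scale of d. Here d is taken in raw-score SDs unless noted.

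**1. The plan's own figures.**
- 200/(1 − 0.20) = 250, as planned.
- With d = 0.45 on the change-score SD, or equivalently r = 0.5 on the raw-score SD, power at 100 per arm is 0.886 (noncentral t; 0.889 by normal approximation). This agrees with the stated value above 0.80.
- With d in raw-score SDs, power above 0.80 needs r of at least about 0.36. The value above 0.90 stated for the interaction needs r of at least about 0.52.

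**2. Variances, equal SDs, no clustering, in units of the raw-score variance.**
- Change score: 2(1 − r).
- Baseline-adjusted: 1 − r².
- Ratio adjusted/change: (1 + r)/2, so the share of precision lost is (1 − r)/2.

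| r | Ratio | Loss | Power, change | Power, adjusted |
|---|---|---|---|---|
| 0.3 | 0.65 | 35% | 0.763 | 0.913 |
| 0.4 | 0.70 | 30% | 0.824 | 0.933 |
| 0.5 | 0.75 | 25% | 0.886 | 0.955 |
| 0.6 | 0.80 | 20% | 0.943 | 0.977 |
| 0.7 | 0.85 | 15% | 0.983 | 0.993 |

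Powers use the noncentral t with standardised effect 0.45/√(2(1 − r)) or 0.45/√(1 − r²). The normal approximation gives slightly higher values: 0.767 and 0.916 at r = 0.3. At r = 0.5, the sample needed for 80% power falls from 78 to 59 per arm (normal approximation).

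A simulation of 20,000 trials at each of r = 0.3, 0.5 and 0.7 gave variance ratios of 0.64, 0.77 and 0.85. The powers were 0.757 and 0.911, 0.889 and 0.954, and 0.984 and 0.993.

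**3. Unequal SDs.** The adjusted variance is k²(1 − r²) and the change-score variance is 1 + k² − 2rk, so the loss is (1 − rk)²/(1 + k² − 2rk). At r = 0.5:
- k = 0.8: 0.36/0.84 = 43%
- k = 1.2: 0.16/1.24 = 13%
- k = 1.3: 0.1225/1.39 = 9%

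**4. Chance imbalance.** With 125 randomised per arm, the standard error of the T1 difference is √(2/125) = 0.126 SD. At r = 0.5 and equal SDs, an imbalance of one standard error shifts the difference of changes by (1 − 0.5) × 0.126 = 0.063 SD. That is 14% of the planned 0.45. Adjustment removes this shift.

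**The case against.** **The model is not fully specified.** A reader might infer that the mixed model estimates a separate T1 mean in each arm. The article does not say so. A longitudinal model with a common T1 mean reports its effect as the same difference of changes, at about the precision of covariate adjustment. The quoted contrast therefore does not force the loss, and parameterisation is often left to an analysis plan. This stands. What remains is that the ANOVA used for power is the unconstrained form, and that the article neither adopts nor excludes a constraint. A sentence is needed to say which model is meant.

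**The size is unknown.** A reader might quote a loss of a quarter. That figure is exact only at r = 0.5 with equal SDs and no clustering, and the article supports none of these. Entry limits on HADS depression and on diagnostic severity could compress the baseline spread, giving k above 1 and a smaller loss. If d is in change-score SDs, planned power is 0.886 whatever r is.

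**Nothing stated is wrong.** A reader might infer bias or inadequate power. The contrast is unbiased over randomisations, and its standard error already includes ordinary chance imbalance. At r = 0.5, power is above 0.80 with or without adjustment. This stands too.

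**Clustering.** A reader might infer that the gain would offset clustering within the groups of four, which the sample-size section does not mention. The article gives no intraclass correlation to support that, and clustering shrinks the gain: at r = 0.5 and an assumed post-treatment value of 0.05 to 0.10, the loss is 22% to 19%.

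**Timing of T1.** T1 follows allocation, and adjustment assumes that allocation does not affect T1. The article says participants learn their arm in the first group session, after T1. The planned contrast needs the same assumption to capture the whole treatment effect, so this point gives no reason to move T1.

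**Conclusion.** The point holds as an improvement in efficiency, not as an error. The primary effect is read and powered as a difference of changes, with no stated adjustment for T1 PHQ-9 and no stated common T1 mean.

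If the model is unconstrained, as the powered ANOVA is, the precision lost is 15% to 35% for r from 0.7 to 0.3, assuming equal SDs and no clustering. At r = 0.5 it is about 9% to 43% over SD ratios of 1.3 to 0.8. The gain in power is largest where the plan is most fragile: at r = 0.3, with d in raw-score SDs, the planned contrast falls below 0.80 and the adjusted one is above 0.90. If the intended model already has a common T1 mean, nothing is lost and only the wording needs completing.

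**What to change.** In Statistical analysis sub-study 1, state that the primary linear mixed model does one of the following:
- enters T1 PHQ-9 as a covariate, with T2 to T7 as outcomes; or
- keeps T1 among the outcomes and constrains its mean to be equal across arms.

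Name the baseline-adjusted T6 difference between arms as the primary estimate. Treat the MADRS, GAS and SPWB in the same way, each with its own T1 value and with T6 and T7 as outcomes. Carry the same structure into the imputation model, which the section already requires to be compatible with the analysis model. It would also help to state the assumed pre-post correlation and the SD to which d = 0.45 refers.

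Adding the T0 ratings of depression severity and anxiety as fixed covariates is optional, since nothing in the article allows their gain to be estimated.

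The cost is a few sentences, with no new data and no change of procedure.
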